### Baseline health characteristics

3.2

A significant portion of participants (59.8 %) reported being overweight during childhood, and 63.6 % identified decreased physical activity as a key factor in their weight gain next to poor dietary habits (58.0 %) and life changes such as pregnancy, marriage, or job transitions (51.1 %). Additionally, hormonal changes, particularly during menopause, were cited by 28.4 % of participants. The main motivators for participants' weight loss efforts were to improve overall well-being and body image (96.6 %) and to enhance physical health (89.8 %). Many participants also sought to reduce pain (51.1 %) and increase physical fitness or muscle strength (78.4 %). Some aimed to be role models for their children or to better engage in hobbies (3.4 %).

Most (96.6 %) participants had previously attempted weight loss, with 67.1 % of participants indicating more than 10 years of experience in weight management efforts. The most common methods included dietary changes (89.4 %), physical activity (30.6 %), and behavioral therapy (34.1 %). However, 91.8 % experienced weight regain. The most frequently reported barriers to successful weight management included lack of activity (81.8 %), challenges with eating behaviors (56.8 %), and physical hunger (19.3 %). Psychological factors, such as depression and other mental health conditions, were reported by 21.6 %, and 26.1 % indicated health-related problems that limited their ability to exercise (see Table 3).

Medical history revealed a high prevalence of obesity-related comorbidities. The mean BMI was 40.1 ± 6.1 kg/m^2^ (see Table 4), with 48.5 % classified as having grade III obesity (BMI > 40) compared with the national obesity rate of 23.3–23.9 % (Blüher, 2019). The mean baseline waist circumference was 123.6 ± 15.2 cm, indicating a high level of visceral fat among participants and corresponding to the high prevalence of hypertension (51.8 %), diabetes mellitus (21.8 %) and dyslipidemia (30.5 %). Further conditions included sleep apnea (9.4 %), gastroesophageal reflux disease (27.1 %), and osteoarthritis, particularly in the knees (25.0 %). Additionally, 20.5 % of participants were diagnosed with fatty liver disease, and 10.7 % reported joint-related diseases such as rheumatism.

**Table 4 t0020:** Medical and family history and joint complaints of the baseline population (98 German adults), assessed at the start of the HAPpEN trial in May/June 2023.

Medical history		baseline population
**Weight**		117.5 ± 22.0 kg (98)
**Height**		170.6 ± 7.5 cm (97)
**Waist circumference**		123.6 ± 15.2 cm (88)
**BMI**^**1**^ Obesity Grade I (BMI 30.0–34.9) Obesity Grade II (BMI 35.0–39.9) Obesity Grade III (BMI >40)		40.1 ± 6.1 kg/m^2^ (97) 22.7 % (22) 28.9 % (28) 48.5 % (47)
**Blood Pressure (systolic/diastolic)**		134.8/85,6 ± 13.7/9,0 mmHg (93)
**Heart Rate**		81.0 ± 12.9 beats/min (94)
**Comorbidities** Hypertension Diabetes Mellitus Reflux Dyslipidemia Uric acid metabolism disorder Myocardial infarction Vascular diseases Lung diseases Sleep apnea Hypothyroidism Kidney diseases Urinary incontinence Gallstone disease Chronic inflammatory bowel disease Fatty liver Joint diseases/rheumatism Knee osteoarthritis Hip osteoarthritis Spinal disc herniation Cervical disc herniation Thoracic disc herniation Lumbar disc herniation Degenerative spine syndrome Degenerative cervical spine disease Degenerative lumbar spine disease Shoulder syndrome Spinal canal stenosis Depression/depressive mood Other psychological conditions Anxiety disorders Burnout Cancer Breast cancer Thyroid cancer Other conditions: skin diseases (psoriasis, neurodermatitis), scoliosis, hip dysplasia, abdominal hernia, neurological disorders (multiple sclerosis, fatigue syndrome), allergies/hay fever, Factor V disorder, post-Coronavirus Disease syndrome, migraines, tinnitus, lymphatic diseases (lymphedema), fibromyalgia		51.8 % (44) 21.8 % (19) 27.1 % (23) 30.5 % (25) 10.7 % (9) 7.0 % (6) 5.8 % (5) 9.3 % (8) 9.4 % (8) 16.7 % (14) 4.6 % (4) 17.2 % (15) 13.8 % (12) 5.9 % (5) 20.5 % (17) 10.7 % (9) 25.0 % (21) 9.5 % (8) 18.6 % (16) 3.6 % (3) 1.2 % (1) 9.6 % (8) 22.1 % (19) 5.3 % (4) 5,3 % (4) 11.8 % (10) 6.0 % (5) 20.0 % (17) 11.1 % (9) 6.3 % (5) 2.5 % (2) 7.0 % (6) 5.8 % (5) 1.2 % (1) 17.2 % (15)
**Physical examination**		baseline population
**Auscultation of Thorax** Rhythmic hear rhythm Clear heart sound Additional heart sounds / others Diminished breath sounds Stridor / obstructive breath sounds		100 % (96) 96.9 % (93) Systolic (3rd intercostal room left) (1), tachycardia (1), paroxysmal atrial fibrillation (1) 1.0 % (1) 2.4 % (2) / 2.4 % (2)
**Abdominal Examination** Soft / distended abdominal wall tenderness Normal / pathological bowel sounds Regular bowel history Constipation / Diarrhea / irregular		98.9 % (94) / 1.1 % (1) 2.1 % (2) 98.9 % (94) / 1.1 % (1) 77.8 % (70) 8.9 % (8) / 10.0 % (9) / 3.3 % (3)
**Neurological Examination** Symmetric / increased / decrease muscle tone Unremarkable strength assessment Intact / pathological sensation		96.8 % (90) / 2.2 % (2) / 1.1 % (1) 100 % (85) 81.5 % (75) / 18.5 % (17)
**Family medical history** Overweight/obesity in the family Diabetes mellitus in the family Hypertension in the family Dyslipidemia in the family Myocardial infarction/sudden cardiac death in the family Arteriosclerosis/vascular occlusion in the family Stroke in the family Kidney disease in the family Depression in the family Cancer in the family		81.2 % (69) 52.3 % (46) 76.5 % (65) 22.5 % (18) 44.2 % (38) 44.4 % (36) 29.8 % (25) 26.2 % (22) 29.3 % (24) 52.3 % (46)
**Joint complaints**		baseline population
General physical complaints		82.4 % (85)
Joint complaints in the past 12 months		83.9 % (87)
Joint complaints in the last 24 h		51.2 % (86)
Pain in the last 24 h Mild/Moderate/Severe	Shoulder	Left side: 11.2 % / 7.1 % / 0.0 % (98) Right side: 13.3 % / 5.1 % / 1.0 % (98)
	Elbow	Left side: 4.1 % / 1.0 % / 0.0 % (98) Right side: 6.1 % / 1.0 % / 1.0 % (98)
	Wrist	Left side: 6,1 % / 3,1 % / 0,0 % (98) Right side: 4.1 % / 5.1 % / 0.0 % (98)
	Finger joints	Left side: 13.3 % / 4.1 % / 0.0 % (98) Right side: 11.2 % / 4.1 % / 1.0 % (98)
	Hip	Left side: 8.2 % / 7.1 % / 3.1 % (98) Right side: 10.2 % / 4.1 % / 5.1 % (98)
	Knee	Left side: 11.2 % / 14.3 % / 1.0 % (98) Right side: 13.3 % / 14.3 % / 4.1 % (98)
	Ankle	Left side: 10.2 % / 9.2 % / 0.0 % (98) Right side: 6.1 % / 11.2 % / 0.0 % (98)
	Toe joints	Left side: 6.1 % / 4.1 % / 0.0 % (98) Right side: 6.1 % / 3.1 % / 0.0 % (98)
Signs of inflammation (top) Full mobility (bottom)	Shoulder	Left side: 1.1 % (93) / Right side: 0.0 % (93)
		Left side: 92.0 % (87) / Right side: 93.0 % (86)
	Elbow	Left side: 0.0 % (93) / Right side: 0.0 % (92)
		Left side: 98.8 % (83) / Right side: 98.8 % (83)
	Wrist	Left side: 0.0 % (94) / Right side: 0.0 % (93)
		Left side: 96.4 % (84) / Right side: 95.2 % (84)
	Hip	Left side: 1.1 % (92) / Right side: 0.0 % (92)
		Left side: 83.3 % (84) / Right side: 86.7 % (83)
	Knee joint	Left side: 3.3 % (92) / Right side: 4.3 % (93)
		Left side: 88.0 % (83) / Right side: 89.3 % (84)
	Ankle joint	Left side: 0.0 % (93) / Right side: 0.0 % (93)
		Left side: 100 % (83) / Right side: 100 % (83)
Pain (top) Movement restriction (bottom)	Cervical spine (C-spine)	13.3 % (90)
		15.9 % (88)
	Thoracic spine (T-spine)	4.4 % (90)
		11.4 % (88)
	Lumbar spine (L-spine)	29.8 % (94)
		33.7 % (89)

^1^BMI, body mass index

Physical examination showed normal heart rhythm in all participants, although 2.4 % exhibited abnormal respiratory sounds. Abdominal distension (1.1 %), tenderness (2.1 %), constipation (8.9 %) and diarrhea (10.0 %) were reported. Neurological assessments demonstrated symmetrical muscle tone in 96.8 % and intact sensory function in 81.5 %. In terms of family history, 81.2 % of participants reported a familial predisposition to overweight or obesity. Hypertension was also prevalent within families, affecting 76.5 % of participants' relatives. Moreover, 52.3 % had a family history of diabetes mellitus, and 44.2 % of heart disease, including myocardial infarction or sudden cardiac death. Notably, 29.3 % had a family history of depression, and 52.3 % reported cancer among family members, further highlighting the genetic and environmental risk factors for both metabolic and psychological conditions within this population (see Table 4).

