**Results:**

The baseline cohort (mean age: 46.9 ± 11.8 years, 74.1 % female) exhibited high obesity rates (mean BMI: 40.1 ± 6.1 kg/m^2^), with 48.5 % classified as grade III obese. Common comorbidities were hypertension (51.8 %), dyslipidemia (30.5 %) and diabetes (21.8 %). Chronic joint paint, mainly in the knees and hips, affected up to 82.4 %. A familial aggregation of obesity, diabetes, and cardiovascular diseases was noted, alongside behavioral challenges such as lack of physical activity (81.8 %) and unhealthy eating habits (56.8 %).

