### Measures

2.5

Primary outcomes include BMI, body weight, waist circumference, blood parameters (e.g. Hemoglobin A1c, lipid metabolism and uric acid), blood pressure and heart rate. Secondary outcomes comprise:•Quality of life (Morfeld and Bullinger, 2008), wellbeing, anxiety (Spitzer et al., 1999) and disease burden (e.g. medication, comorbidities, sleeping behavior)•Nutrition, health and physical activity literacy as well as health behavior change for an improved understanding of patients' personal health status (Spitzer et al., 1999; Westenhöfer et al., 2003; Bull et al., 2009; Pfeiffer et al., 2020)•Benefit and effectiveness of social interaction (Borek et al., 2019; Carrillo-Álvarez et al., 2019; Nackers et al., 2015)•Acceptance, efficiency, user-friendliness and -experience of digital therapy support by evaluating self-reported application usage frequency and its most relevant features (Cheah et al., 2022; Laugwitz et al., 2008; Sekhon et al., 2022)•Economic evaluation through literature-based modeling of the costs and their assessment relative to the generated benefits

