### Statistics

2.6

BMI and body weight will be compared between the patients in the trial and those receiving current obesity standard care. Furthermore, outcomes will be analyzed at baseline and after six and 12 months, using paired *t*-tests, analysis of variances, Cochran's Q or Friedman test (see Table 2). Data distribution will be analyzed using Shapiro-Wilk normality test and histograms.

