### Baseline demographic characteristics of the trial population

3.1

The baseline population consisted of 98 German participants with a mean age of 46.9 ± 11.8 years, slightly higher than the national average and average from the federal stat of Bavaria (Statistische Bibliothek, 2022). Most participants were female (74.1 %) and married, cohabitating with their spouse (64.3 %) (see Table 3). Compared to national averages, higher proportions had secondary education (43.5 %) and professional training (62.2 %), but fewer held high school diplomas (20.0 %) or university entrance qualifications. The majority (83.3 %) were employed, with 14.5 % working in shift-based jobs.

**Table 3 t0015:** Demographic characteristics and weight history of the baseline population (98 German adults), assessed at the start of the HAPpEN trial in May/June 2023.

Demographic characteristics	baseline population	Weight history	baseline population
**Gender** Female/Male	74.1 % (63) / 25.9 % (22)	**Childhood Overweight**	59.8 %
**Age**	46.9 ± 11.8 years (83)	**Previous Weight Loss Attempts**	96.6 % (84)
**Practice Affiliation** Oberlandärzte Marktleugast [name]/[name] Presseck [name]/[name] Untersteinach [name]/[name] Thurnau [name] Kasendorf [name] Stadtsteinach	52.0 % (51) 5.1 % (5) 6.1 % (6) 16.3 % (16) 13.3 % (13) 7.1 % (7)	**Years Spent on Weight Reduction** 10 years five to nine years two to four years < two years	67.1 % (55) 18.3 % (15) 7.3 % (6) 7.3 % (6)
**Marital Status** Single, living alone Single, living with a partner Married, living with spouse Married, living separately Divorced Widowed	13.1 % (11) 14.3 % (12) 64.3 % (54) 1.2 % (1) 6.0 % (5) 1.2 % (1)	**Causes/Triggers of Weight Gain** Life changes: career change, relocation, retirement Changes in family environment: pregnancy, children, marriage, divorce Decreased physical activity Unbalanced diet Menopause/hormonal changes Medications/underlying health conditions Increased alcohol consumption Smoking cessation Other: stress, fieldwork, acute illness/injury, bullying, exam situations	13.6 % (12) 51.1 % (45) 63.6 % (56) 58.0 % (51) 28.4 % (25) 34.1 % (30) 5.7 % (5) 17.0 % (15) 13.6 % (12)

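### Baseline waist circumference, a primary outcome, is missing for 10 of 98 patients, and the named tests in their usual form would drop these patients from the waist analysis

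*Protocol article*

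**What the plan says.** Section 2.5 (Measures) opens its outcome list with "Primary outcomes include BMI, body weight, waist circumference" and goes on to blood parameters, blood pressure and heart rate. Table 2 schedules waist at enrolment, month 6 and month 12, and assigns analysis of variance to that row. Section 2.6 (Statistics) says that outcomes at the three time points will be analysed "using paired *t*-tests, analysis of variances, Cochran's Q or Friedman test", and refers to Table 2.

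Table 4 gives waist as "123.6 ± 15.2 cm (88", weight as "117.5 ± 22.0 kg (98" and BMI as "40.1 ± 6.1 kg/m^2^ (97". For these means the bracketed number is the number of patients measured.

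On the cohort, section 3.1 says: "The baseline population consisted of 98 German participants". The abstract's results begin: "The baseline cohort (mean age: 46.9 ± 11.8 years, 74.1 % female". Table 3 shows sex as "74.1 % (63) / 25.9 % (22", where the brackets are counts, and gives age with n = 83.

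**The concern.** The gap is present at baseline, so it comes on top of any later dropout. A paired t-test of change from baseline needs both values. Classical repeated-measures analysis of variance, Cochran's Q and the Friedman test need every visit. A patient without a baseline waist value therefore contributes nothing to any of them, whatever is measured later.

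Two things are at stake. Waist change would rest on fewer patients than weight change, so two primary outcomes set side by side would not describe quite the same people. And if the 10 unmeasured patients differ from the rest, for example in body size or in practice, the waist result carries a selection that the weight result does not.

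The cohort description has a related, smaller weakness. Percentages that hold for about 82 to 87 patients are given in the text as describing 98.

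**Working it through.** **Inputs.** Cohort 98 (section 3.1). Numbers measured at baseline (Table 4): waist 88, weight 98, BMI 97, blood pressure 93, heart rate 94. Sex 63 and 22, age n = 83 (Table 3). Hypertension 44, printed as 51.8 % (Table 4). The article gives no alpha, power or sample-size figure, so there is no planned precision to reproduce.

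**1. Missing baselines among the primary outcomes.**
- Waist: 98 − 88 = 10; 10/98 = 10.2 %
- Blood pressure: 98 − 93 = 5; 5.1 %
- Heart rate: 98 − 94 = 4; 4.1 %
- BMI: 98 − 97 = 1; 1.0 %
- Weight: 0

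Waist has the largest gap of these.

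**2. Precision.** With a fixed standard deviation of change, the standard error is proportional to 1/√n. For 88 against 98 the ratio is √(98/88) = 1.055, that is 5.5 % larger. This assumes that all 98 attend later, or that later attendance is proportionally the same in the 88 and the 10. If the 10 drop out anyway, the extra loss is smaller.

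For illustration, assume two-sided alpha 0.05 and 80 % power. The detectable standardised paired change is (1.960 + 0.842)/√n:
- n = 98: 0.283
- n = 88: 0.299

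**3. Selection.** If the mean change in the 10 differs from that in the 88 by d standard deviations, the complete-case mean is off by (10/98) × d. The article gives no value for d, nor its sign. For assumed values:
- d = 0.25: 0.102 × 0.25 = 0.026 SD
- d = 0.5: 0.102 × 0.5 = 0.051 SD

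The standard error at n = 88 is 1/√88 = 0.107 SD, so even d = 0.5 gives about 0.5 of a standard error.

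**4. Denominators of the cohort figures.** The printed sex figure reproduces on 85 patients and not on 98:
- 63 + 22 = 85; 63/85 = 74.1 %
- 63/98 = 64.3 %

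Hypertension behaves the same way: 44/85 = 51.8 %, against 44/98 = 44.9 %. Diabetes (19, 21.8 %) and dyslipidemia (25, 30.5 %) reproduce on 87 and 82. Extreme bounds over all 98, putting all 13 missing patients in one category or the other:
- Female: 63/98 = 64.3 % to 76/98 = 77.6 %
- Hypertension: 44/98 = 44.9 % to 57/98 = 58.2 %

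**5. How many patients could lack every form.** The items on causes, reasons and barriers reproduce on 88 (for example 85/88 = 96.6 % and 72/88 = 81.8 %). So at least 88 patients answered something, and at most 98 − 88 = 10 returned no questionnaire. Lower denominators on other items are item non-response.

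**The case against.** The strongest case against is that missing-data handling normally belongs in the full protocol or SAP, and a short statistics section in an article neither prescribes complete-case analysis nor says that patients will be dropped. Table 2 assigns waist to an analysis of variance of unspecified form, and a mixed-model version would keep the 10 patients. This stands in part: the silence is not itself the finding. What remains is that the methods actually named, read in their usual form, lose patients whose gap is already known, and that a better method of the same kind is available.

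It is also fair that n = 88 is printed beside the waist mean, that weight and BMI are essentially complete, that the waist set contains about 90 % of the weight set, and that the loss of precision is modest. All of this stands.

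A reader might infer more than the documents support:
- *That 10 to 15 patients returned no baseline questionnaire.* The item denominators do not show this. At most 10 can lack every form.
- *That quality-of-life or literacy results will cover only about 85 responders.* Tables 3 and 4 give no baseline n for these outcomes.
- *That the patients with missing values are less engaged, so that benefit will be overstated.* Nothing in the article describes them. The bias figures above rest on an assumed difference and could go either way.
- *That the true share of women is far from the printed one.* The outer bounds require all 13 missing patients to be of one sex.

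**Conclusion.** The point holds as a limited one about the waist analysis. Ten of 98 patients (10.2 %) have no baseline for a primary outcome, and the named methods in complete-case form would exclude them. The cost is a standard error about 5.5 % larger with full follow-up, plus a possible selection whose size and direction the article does not let one judge. This rests on reading analysis of variance in its classical form. If a likelihood-based mixed model is already meant, stating so largely settles the matter. Blood pressure and heart rate share the problem to a lesser degree (5 and 4 patients). Weight and BMI are practically unaffected, and no claim is made about quality of life or literacy.

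The missing denominators in the abstract and the results text are a secondary reporting point.

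**What to change.** 1. Analyse waist with a linear mixed model in which baseline, month 6 and month 12 are all outcomes, so that the 10 patients contribute their later values. Alternatively, multiply impute the missing baselines from weight or BMI at all visits and the later waist values, adding sex where it is recorded. Use the same approach for blood pressure and heart rate.
2. Report the complete-case waist result as a sensitivity analysis.
3. Compare baseline weight in the 88 and the 10. Weight is complete, so this gives a direct if limited look at selection.
4. Complete age from practice records, since it was an eligibility item, and sex and diagnoses where the records allow. Otherwise print the true n beside these figures in the abstract and sections 3.1 and 3.2.

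The cost is a short addition to the analysis and a records look-up in six practices. The downside is the assumption that waist is missing at random given the variables in the model, which is why the complete-case result should stay visible.

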### Baseline musculoskeletal health

3.3

Chronic joint pain was common, with 82.4 % of participants reporting musculoskeletal discomfort, and 83.9 % experiencing joint pain over the past year (see Table 4). Additionally, 51.2 % had joint pain in the 24 h prior to assessment. Pain was primarily concentrated in the knees, hips, and shoulders. Mild knee pain was reported by 11.2 % (left) and 13.3 % (right) of participants, while moderate pain affected 14.3 % for both knees. Shoulder pain was present in 18.3 %, and hip pain affected 15.3 % (left) and 14.3 % (right). Elbow, wrist, and finger pain were less common, and ankle and toe joints were minimally impacted. Inflammation was most frequent in the knees (3.3 % left, 4.3 % right), with minimal signs in the shoulders and hips. Mobility remained largely intact for most joints, with over 90 % retaining full movement in shoulders, wrists, elbows, and ankles. However, mobility restrictions were more evident in the hips (16.7 % left, 13.3 % right) and knees (12.0 % left, 10.7 % right), while the lumbar spine showed the greatest impairment, with 29.8 % reporting pain and 33.7 % noting restricted movement.

## Discussion

4

Obesity poses a global health challenge necessitating a multifaceted approach. Our trial examines evidence supporting long-term obesity management, emphasizing a personalized, holistic, general practitioner-centered approach in rural areas. By addressing the unique socio-cultural and geographical challenges faced by these populations, HAPpEN leverages general practitioners as key facilitators recognizing various contributing factors such as genetics, metabolism, medical history, lifestyle, and psychosocial elements (Ahima and Lazar, 2013). Continuous education and support provided by general practitioners have been shown to empower patients, enhancing health literacy and fostering sustained improvements in weight management (Burke et al., 2011; Moore et al., 2019). HAPpEN's general practitioner-centered therapy integrates dietary and physical activity guidance, and evidence-based behavioral interventions, ensuring that general practitioners are equipped to deliver personalized, non-judgmental care effectively, seen to be lacking in the past (Rubino et al., 2021). Moreover, this trial aligns with existing literature on weight history, motivators, and barriers to weight loss, while providing additional insight into rural settings. A high prevalence of childhood overweight reinforces previous findings linking early obesity to adulthood, while decreased exercise and poor dietary habits emerge as significant contributors to weight gain (Simmonds et al., 2016). Motivators such as improved well-being and physical health echo results from other studies. Additionally, the high rate of weight regain reflects the complexities of long-term weight management and the associated challenges, including lack of physical activity, difficulties with eating behaviors and psychological factors (Trujillo-Garrido and Santi-Cano, 2022). Our data capture district-level rural health characteristics absent from broader datasets (Mensink et al., 2013). This nuanced profile supports tailored health interventions in rural settings.

Importantly, the program incorporates smartphone-based tools, which have proven to enhance communication and flexibility among patients and therapists, by fostering interdisciplinary collaboration peer support and improve empowerment, knowledge, adherence and clinical outcomes at reduced costs (Burke et al., 2011; Ufholz and Werner, 2023). Our trial introduces a smartphone-based, stepwise self-monitoring diary for tracking dietary habits and physical activity while emphasizing motivational and self-regulatory factors essential for sustainable lifestyle changes (Palmeira et al., 2023). This supports the comprehensive and personalized approach to obesity management, especially for rural areas, with limited health-related resources. In this context, the formative survey conducted in rural Kulmbach was instrumental in addressing the region-specific intervention needs.

The baseline data of the HAPpEN cohort indicates a high prevalence of obesity and comorbidities, with a higher average BMI and greater proportion of participants with grade III obesity, highlighting the program's success in engaging patients with significant treatment needs.

Our data provide insights into challenges of obesity management in German rural settings. Given the structural weakness in rural healthcare, including a shortage of nutritionists and psychotherapists, HAPpEN maximizes available resources by having general practitioners take on a central advisory role, that they have inherent by nature from patient's perspective (Wangler and Jansky, 2023). Additionally, HAPpEN acknowledges the fact that fighting obesity is more effective in like-minded groups (Street and Avenell, 2022) by offering sporting groups, a digital forum to exchange efforts or recipes and foster participant exchanges to enhance self-efficacy and learning.

The flexibility of the pragmatic approach in HAPpEN allows for intervention adaptation and strategy identification, though the lack of a non-intervention group may limit precise impact assessment and the ability to attribute observed changes in outcomes directly to HAPpEN. The program also primarily targets patients with a BMI ≥ 30 kg/m (Blüher, 2019), excluding overweight individuals who may benefit from early intervention.

